**4.8 Initial Procedures and Participant Recruitment**

Participants will be recruited from patients presenting to the emergency room at [name] Netto Hospital (HMACN) with shoulder trauma and suspected fractures. All patients will receive treatment according to the hospital's standard protocol.

The cases will be evaluated by the on-call orthopedic team, which will notify the research team. In the emergency room, the examining researchers will request standard imaging tests, including anteroposterior, scapular profile, and axillary shoulder radiographs, and CT scans when indicated. Preoperative tests, including complete blood count, coagulation profile, blood typing, serum levels of sodium, potassium, urea, creatinine, glucose, electrocardiogram, and chest X-rays (posteroanterior and lateral views), will also be requested. Echocardiograms and consultations with other specialties will be requested when necessary.

Potential study inclusion will be determined only after clinical and radiographic evaluations confirm eligibility. Participants will receive verbal and written explanations regarding the study's objectives and methods. Those who agree to participate will sign the informed consent form (Appendix 1).

**4.9 Medication Prescription**

During hospitalization, analgesic prescriptions will include dipyrone 1g IV every 6 hours and tramadol hydrochloride 100 mg IV every 8 hours, maintained for the first 24 hours. If rescue analgesics are needed, the first option will be to administer tramadol hydrochloride 100 mg IV every 6 hours. Morphine sulfate will be the second rescue drug, administered at a dose of 2 mg IV up to every 8 hours. Patients will be reassessed for adjustments to the standard analgesic regimen, transitioning to "as needed" prescriptions for opioids when possible. All analgesic drug use will be documented. Corticosteroids or anti-inflammatory drugs will not be prescribed.

Upon discharge, participants will be prescribed dipyrone 1g orally every 6 hours for 5 days and tramadol hydrochloride 50 mg orally every 8 hours (if needed) for a maximum of 5 days. Participants will be instructed to use tramadol hydrochloride only if pain persists with dipyrone or in cases of moderate pain (4–7 on the pain scale). Participants reporting anti-inflammatory or corticosteroid use will be excluded from statistical analysis, and the case will be documented and discussed.

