**Photobiomodulation**

Photobiomodulation (PBM), formerly known as low-level laser therapy, is defined as the use of light sources to stimulate healing, relieve pain, and reduce inflammation (Hamblin, 2017). This therapy is safe, minimally invasive, and has no side effects (Hamblin, 2017; Sharma et al., 2023). The most commonly used sources for PBM are lasers and LEDs (light-emitting diodes) of low intensity or power in the red (600–700 nm) and near-infrared (770–1200 nm) wavelengths.

PBM action is based on light absorption by cellular chromophores, which can be categorized into three groups: mitochondrial cytochromes (proteins bound to the inner mitochondrial membrane, such as cytochrome C oxidase); opsins (3 and 4); and heat- or light-sensitive calcium ion channels, and nano-structured water clusters (Sharma et al., 2023). Light-sensitive ion channels are activated by light absorption by opsins, while mitochondrial cytochromes absorb red and near-infrared wavelengths. Light above 980 nm is likely absorbed by nano-structured water clusters, activating transient receptor potential (TRP) ion channels. Heat-sensitive TRPs may also be activated by minor temperature changes (Sharma et al., 2023).

Red or infrared light absorbed by mitochondrial cytochrome C oxidase may dissociate the inhibitory nitric oxide associated with it, increasing enzymatic activity, electron transport, mitochondrial membrane potential, and ATP production (Sharma et al., 2023). Another possible explanation for PBM effects is the activation of light-sensitive ion channels, allowing calcium influx into cells or mitochondria. Both pathways activate mitochondrial metabolism and numerous signaling pathways, such as reactive oxygen species (ROS), cyclic AMP, nitric oxide, and calcium ions. These pathways lead to transcription factor activation, enhancing gene expression related to protein synthesis, cell migration, proliferation, anti-inflammatory signaling, anti-apoptotic proteins, and antioxidant enzymes (de Freitas & Hamblin, 2016; Sharma et al., 2023).

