The same group of authors assessed the effect of PBM (904 nm, 25W pulse peak, 60 kHz, 60 mW average power, 7.2 J per session, 1.2 J per point), combined with exercises, applied after immobilization removal in 50 patients with distal radius fractures treated conservatively (non-surgically). The triple-blind RCT evaluated standardized wrist function and pain perception questionnaires, nighttime pain, and analgesic consumption at 4, 8, 12, and 26 weeks. Nighttime pain and analgesic use were also assessed after 7 weeks. The PBM group showed significantly better outcomes in standardized function and pain perception questionnaires at 8, 12, and 26 weeks. Nighttime pain and analgesic use were significantly lower in the PBM group between 7 and 26 weeks (Saebo et al., 2022).

Jana Neto et al. (2023) evaluated the effect of PBM with LEDs on the healing process of soft tissue injuries associated with surgically treated tibia fractures. The study included 27 adult individuals awaiting resolution of soft tissue injuries before definitive surgery. PBM (144 LED diodes at wavelengths of 420 nm, 660 nm, and 850 nm, 3 J per point, for 10 minutes) was applied daily until the soft tissues were ready for definitive surgery. The control group was treated with inactive devices identical in appearance. The PBM-treated group showed better daily healing rates, greater average daily reduction in pain scores, four times fewer infections at the pin sites of external fixators, and faster resolution (10 days earlier). No adverse effects were reported.

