**Exclusion Criteria:**

- Individuals with prior injuries or sequelae in the shoulder or scapular girdle, or motor deficits due to central or peripheral neurological injuries.
- Patients with pathological fractures.
- Participants with postoperative infection or implant loosening.
- Those with ipsilateral fractures in other areas of the limb.
- Patients with neurovascular injuries causing sensory deficits at the injury site.
- Individuals with local or systemic conditions contraindicating surgical intervention or complicating the postoperative period.
- Participants with a history of photosensitivity.
- Individuals with neurological or psychiatric disorders.
- Those with proliferative or infectious skin lesions in the shoulder area where LED light will be applied.
- Participants who used anti-inflammatory medications within 5 days prior to the trauma.
- Pregnant individuals.
- Participants who experience surgical complications, such as neurological or vascular injuries or fracture line extension during surgery, as they will not meet the desired progression criteria.

Such participants will be excluded from statistical analyses but will have their data collected and documented.

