**4.7 Randomization and Allocation Concealment**

The sequence generation and envelope preparation will be conducted by a researcher not involved in the study.

Participants will be randomly assigned to the two experimental groups using a random sequence generator (<https://www.randomizer.org/tutorial/>), with the option for block randomization of six participants, forming seven blocks. Opaque envelopes will be numbered sequentially, each containing a sheet with the corresponding experimental group based on the generated order. The envelopes will be sealed and stored in numerical order in a secure plastic container.

Participants meeting all previously described eligibility criteria will be evaluated by four surgeons and included in the study. All participants will undergo the same surgical protocol. The allocation envelope will be opened 24 hours after the surgical procedure when the PBM device is delivered. The device delivery will be performed by the medical resident researcher, who will be aware of the allocations.

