**4.14 Intervention Failure**

Therapy failure will be characterized if any of the following occurs:

1. Inability to apply PBM daily.
2. The participant develops bleeding, sepsis, urticaria, or any discomfort justifying the discontinuation of PBM or placebo PBM.
3. Discontinuation of treatment for any other reason. In these cases, data collected up to that point will be included in the statistical analysis using a mixed-effects regression model.
4. Failure to attend in-person evaluations or respond to scheduled virtual contacts. Data collected up to this point will also be included in the statistical analysis using a mixed-effects regression model.

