**QuickDASH Score Calculation**:

QuickDASH Score=[(Sum of responsesn)−1]×25\text{QuickDASH Score} = \left[\left(\frac{\text{Sum of responses}}{n}\right) - 1\right] \times 25QuickDASH Score=[(nSum of responses​)−1]×25

Where nnn is the number of answered questions.

The QuickDASH will be administered at 1, 2, 4, 8, and 12 weeks post-surgery.

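### Participants are excluded from the analysis for events that arise mostly after randomisation (clearly for anti-inflammatory or steroid use, arguably for infection and implant loosening), which risks biasing the comparison and conflicts with the rule for other discontinuations

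*Protocol*

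**What the plan says.** **Time of allocation (section 4.7).** "The allocation envelope will be opened 24 hours after the surgical procedure when the PBM device is delivered".

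**Follow-up for the primary outcome (section 4.15.1).** "The QuickDASH will be administered at 1, 2, 4, 8, and 12 weeks post-surgery".

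**Drug-use rule (section 4.9).** Directly after the discharge prescriptions: "Participants reporting anti-inflammatory or corticosteroid use will be excluded from statistical analysis, and the case will be documented and discussed".

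**Exclusion criteria (section 4.4).** The list includes "Participants with postoperative infection or implant loosening". Its last bullet covers complications during surgery, and the list closes with: "Such participants will be excluded from statistical analyses but will have their data collected and documented".

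**Other discontinuations (section 4.14).** Where participants stop on grounds not listed separately, the protocol states: "In these cases, data collected up to that point will be included in the statistical analysis using a mixed-effects regression model". The same treatment is given to those who miss visits or contacts. Sepsis, and discomfort that justifies stopping the device, are also listed there as intervention failure.

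**Outcomes affected (section 3.2).** Adverse-event incidence and analgesic consumption are secondary outcomes.

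**The concern.** A randomised comparison is protected only while everyone allocated stays in the analysis, or leaves it for reasons unrelated to arm and prognosis. Taking an anti-inflammatory drug or a steroid during recovery is unlikely to be such a reason, because it tends to follow pain. The protocol's background describes PBM as "the use of light sources to stimulate healing, relieve pain, and reduce inflammation", so on its own hypothesis the trigger may be less common in the active arm. Infection and loosening raise the same difficulty to the extent that they are also excluded.

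Two things are at stake:

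- **Efficacy.** If more poorly recovering participants are removed from control than from PBM, the control mean improves artificially and the estimated effect shrinks.
- **Safety and analgesic use.** The participants removed are among those who would supply the events that these outcomes count.

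**Working it through.** **Step 1. When do the triggers occur?**

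- *Drug use.* Use before the trauma has its own exclusion criterion (within 5 days before trauma). Section 4.9 says that anti-inflammatory drugs and corticosteroids will not be prescribed. What remains is use that the participant reports, chiefly after discharge and so after allocation. The discharge analgesics are prescribed for 5 days, while QuickDASH is collected to week 12.
- *Infection and loosening.* Both are postoperative by definition. They cannot be known when eligibility is confirmed and consent is signed, and mostly arise later than 24 hours.

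**Step 2. Do the sections agree?**

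| Event after allocation | Section | Handling |
|---|---|---|
| Anti-inflammatory or steroid use | 4.9 | Out of the analysis |
| Infection, loosening | 4.4 | Listed exclusion; out of the analysis on one reading |
| Stopping for any other reason, missed visits | 4.14 | Data to that point kept in a mixed-effects model |

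A participant who stops the device because of an infection could fall under 4.4 or 4.14, with opposite results. Section 4.14 does not restore those removed under 4.9.

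**Step 3. The protocol's own figure.** The 21 per group (alpha 0.05, 90% power, 15% loss) cannot be reproduced, because no difference or SD is given. It is compatible with 18 evaluable per arm: 18 × 1.15 = 20.7. This point does not rest on that figure.

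**Step 4. How large could the bias be?** The documents give no exclusion rates, so every input here is an assumption:

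- Each participant has a pain liability with SD 1 and is excluded when it exceeds a threshold c.
- The liability correlates r = 0.5 to 0.7 with QuickDASH within each arm.
- PBM lowers both liability and QuickDASH by s = 0.5 to 0.8 SD.
- A share p of controls is excluded, so c = Φ⁻¹(1 − p).

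Write λ(x) = φ(x)/Φ(x). Removing the upper tail lowers the control mean by r·λ(c) and the PBM mean by r·λ(c + s). The lost part of the effect is therefore

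loss = r × [λ(c) − λ(c + s)].

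Worked case: p = 25%, s = 0.5. Here c = 0.674, λ(0.674) = 0.424 and λ(1.174) = 0.228. PBM exclusions are 1 − Φ(1.174) = 12.0%. With r = 0.5 the loss is 0.098 SD, so 0.50 becomes 0.40. With r = 0.7 it is 0.137 SD, so 0.50 becomes 0.36.

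| Controls excluded | PBM excluded (s = 0.5; 0.8) | Effect lost, s = 0.5 (r = 0.5; 0.7) | Effect lost, s = 0.8 (r = 0.5; 0.7) |
|---|---|---|---|
| 5% (about 1 of 21) | 1.6%; 0.7% | 6.8%; 9.5% | 5.5%; 7.7% |
| 10% (about 2 of 21) | 3.7%; 1.9% | 11.0%; 15.4% | 9.3%; 13.0% |
| 25% (about 5 of 21) | 12.0%; 7.0% | 19.6%; 27.5% | 17.4%; 24.4% |

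**Step 5. Boundary cases.** If the trigger works alike in both arms and the rates are equal, the two λ terms are equal and the bias is 0. If more PBM than control participants are removed, the sign reverses. For example, 10% of PBM against 5% of controls gives r × (0.195 − 0.109), an overstatement of about 0.04 to 0.06 SD.

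**The case against.** **The closing sentence of the exclusion criteria is ambiguous.** It follows the bullet on complications during surgery, which precede allocation, and may refer to that bullet alone. Read across the whole list it would mean collecting trial data on people who never enter, such as pregnant or photosensitive patients. A reader might infer that infection and loosening cases are certainly deleted; the text does not settle this, and section 4.14 points the other way. The objection stands for that limb. It leaves untouched the drug-use rule, which is explicit, and the fact that postoperative events sit among eligibility exclusions.

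**Harm is not erased.** A reader might infer that adverse events vanish. The protocol says that data under section 4.4 are collected and documented, that section 4.9 cases are documented and discussed, and that adverse events and analgesics are recorded at the daily contacts. Descriptive reporting remains possible. What is at risk is the formal analysis, for which no exception is made.

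**Unequal exclusion is not shown.** The documents give no rates by arm. If PBM affects neither trigger nor outcome, there is no bias, so the pain-driven model does not produce a false positive. This stands: unequal exclusion is a risk, not a fact.

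**The infection precedent is weak.** The background cites a trial with "four times fewer infections at the pin sites of external fixators", but that trial had 27 people with tibial fractures and soft-tissue injury. Here fractures are closed and plated internally, and the plate area with a 2 cm margin is not irradiated. It is a reason for caution, not evidence of a difference in this trial.

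**An SAP may exist.** It could define analysis sets, but the protocol is not silent here: it already fixes an exclusion rule.

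**Conclusion.** The drug-use rule in section 4.9 is wrong as written. It removes participants from analysis for an event that arises mostly after randomisation and can depend on treatment, and nothing in the protocol restores them. For infection and loosening, the defect is an unclear rule that conflicts with section 4.14 and must be reconciled.

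The consequence is a risk of bias of unknown size. With the Step 4 assumptions, about 6–15% of the effect is lost at 5–10% control exclusion and 17–27% at 25%. The 25% rate has no basis in the documents and is an upper illustration. Like-for-like exclusion gives no bias. Neither a demonstrated imbalance between arms nor a complete loss of safety information can be claimed from the text.

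**What to change.** 1. Make the primary analysis all randomised participants in their allocated arm, with all observed QuickDASH data.
2. Delete the exclusion from statistical analysis for every event after the envelope is opened, and state that scheduled assessments continue after such events.
3. Restrict eligibility exclusions to facts known before allocation. Move postoperative infection and implant loosening out of that list.
4. Reconcile sections 4.4, 4.9 and 4.14 so that each event has one stated handling.
5. Count infection and loosening in the adverse-event analysis, and anti-inflammatory or steroid use in the analgesic outcome.
6. Keep the present exclusions only as a labelled per-protocol sensitivity analysis.

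The sample size stays at 42 and no clinical rule changes. The cost is protocol wording, some outcome noise from concomitant medication, and an explicit commitment to follow these participants at visits already scheduled. That commitment is needed because section 4.9 promises only that the case is documented and discussed, and section 4.14 keeps data only up to the point of stopping.

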**4.10 Surgical Procedure**

All participants will undergo general anesthesia combined with brachial plexus block and a standard surgical procedure as practiced at the Orthopedics Department of HMACN.

Fractures will be approached using a deltopectoral incision with the patient in a beach chair position. Careful dissection will be performed to avoid excessive exposure of fragments and preserve vascularization. Fragments will be anatomically reduced using indirect maneuvers and temporarily stabilized with Kirschner wires (Biomecânica, Jaú, SP, Brazil). Definitive stabilization will be achieved with an anatomical locked proximal humerus plate (GM Reis, Campinas, SP, Brazil) of 3.5 mm, the gold standard for PHF stabilization (Ratajczak et al., 2019; Oldrini et al., 2022). The plate will be positioned 1 cm below the superior edge of the greater tuberosity and 1 cm lateral to the long head of the biceps tendon.

The reduction, plate positioning, and screw placement will be evaluated intraoperatively using fluoroscopy.

Parte inferior do formulário

[figure not shown]

Figure –Blocked plate. Source: own author.

**4.11 Physiotherapy**

All participants will follow a standardized physiotherapy protocol as suggested by Ratajczak et al. (2019) and the AO Trauma group (<https://www.aofoundation.org/trauma>), detailed below:

**Stage 1: First 3 weeks, starting 24 hours after surgery**

- Immobilization with a sling for the operated limb without weight-bearing.
- Initiation of pendulum exercises.
- Assisted passive movements.
- Avoid external rotation during the first 6 weeks.

**Stage 2: Third to ninth week, provided there are no abnormalities in consolidation or secondary displacement of fragments**

- Assisted active exercises, including flexion and abduction of the shoulder joint.
- Careful active exercises with limb abduction until pain occurs, with no weight-bearing in the first 6 weeks. Gradual weight addition will follow.

**Stage 3: After the ninth week**

- Isotonic, eccentric, and concentric exercises.
- For participants with radiographic fracture consolidation (evaluated at the 12th week) and joint contracture, passive stretching exercises will be recommended under the guidance of an experienced professional.

Participants will attend 30-minute physiotherapy sessions twice weekly for 12 weeks.

**4.12 Photobiomodulation (PBM) Application**

PBM will be administered using LED devices in the form of a shoulder brace. Applications will commence 24 hours after surgery and will continue daily throughout the experimental period. Participants will perform the applications at home, receiving guidance on how to wear and operate the equipment upon hospital discharge, along with written instructions (Appendix 9). Each application will last 10 minutes.

The shoulder brace, manufactured by Cosmedical (Mauá, SP, Brazil), contains 159 red LEDs and 159 infrared LEDs arranged alternately. The area corresponding to the fixation plate, with a 2 cm safety margin added along its entire length, will not be irradiated (LEDs will not be placed there) to avoid potential heating of the plate from energy absorption.

Participants allocated to the control group will receive a device identical to the active one. However, only the activation plug light and sound will turn on when the button is pressed, leaving the internal LEDs deactivated

[figure not shown]

Figure . Design (A) and model (B) of the shoulder brace for PBM application.

Literature reports on the use of PBM after bone fractures indicate the use of red and infrared light sources with varying dosimetric parameters (Table 1), with radiant exposures ranging from 3 to 16 J/cm². The study by Chang et al. (2014), which served as the basis for the sample size calculation in this project, demonstrated positive effects of PBM on functional recovery of wrist and hand fractures using the Quick DASH questionnaire, with a radiant exposure of 9.7 J/cm². Accordingly, this project adopted radiant exposures of 10 J/cm² and 12 J/cm²

| **Wavelength (nm)** | **Power (mW)** | **Irradiance (mW/cm²)** | **Time (sec)** | **Radiant Exposure (J/cm²)** | **Radiant Energy (J) per Point** | **Number of Applications** | **Application Points** | **Results** | **Authors** |
| --- | --- | --- | --- | --- | --- | --- | --- | --- | --- |
| 830 | - | - | - | 8 and 16 | - | Once per day | Sensitive points | Earlier symptom resolution and ambulation | Chauhan & Sarin (2005) |
| 830 | 60 (average power) | 16.2 ± 1 | 600 | 9.7 | 2.5 | 10 | 1 | Pain relief and improved consolidation in conservative wrist fracture treatment | Chang et al. (2014) |
| 808 & 650 | 300 & 100 | 30 ± 20 | 20 ± 30 | 6 ± 3 | 6 ± 3 | 1 | 10 to 12 | Less opioid consumption in tibia fracture treatment | Nesioonpour et al. (2014) |
| 904 | 60 (average power) | 120 | 120 | 3 and 1.2 | 9 | 6 | Improved nighttime pain after 3 weeks; better ROM and grip strength | - |  |
| 904 | 60 (average power) | 120 | - | 1.2 | 9 | 6 | Significant improvement in functional score (PRWHE) after 8, 12, and 26 weeks |  | Jana Neto (2023) |

In the present study, the dosimetric parameters (Table 2) will combine higher and lower energy wavelengths (red and infrared, respectively) with higher and lower penetration depths (infrared and red, respectively), ensuring energy per point and radiant exposures within the limits reported in the literature. To calculate the parameters, the radiant power of each LED was measured using a power meter with a pyroelectric sensor (Coherent, Field Max2 model, Wilsonville, OR, United States).

[figure not shown]

In this study, the dosimetric parameters (Table 2) will allow the combination of photons with higher and lower energy (red and infrared, respectively), greater and lesser penetration (infrared and red, respectively), with energy per point and radiant exposures within the limits reported in the literature. The radiant power of each LED was measured using a power meter with a pyroelectric sensor (Coherent, Field Max2 model, Wilsonville, OR, United States).

